## GLOSSARY OF ABBREVIATIONS

|                 |                                                              |
|-----------------|--------------------------------------------------------------|
| aCSA     | average CSA                                           |
| arCSA    | average relative CSA                                  |
| aLeanCSA | average LeanCSA                                       |
| BASEC    | business administration system for ethical committees |
| CAD      | Computer-aided Design                                 |
| CSA      | cross-sectional area                                  |
| BMI      | body mass index                                       |
| CRF      | case report form                                      |
| C7PL     | C7 plumb line                                         |
| EMG      | electromyography                                      |
| FOPH     | federal office of public health                       |
| FJ       | facet joint                                           |
| HRA      | human research act                                    |
| HRO      | ordinance on human                                    |
| LeanCSA  | CSA of lean muscle in region of interest              |
| LSS      | lumbar spinal stenosis                                |
| LL       | lumbar lordosis                                       |
| MRI      | magnetic resonance imaging                            |
| ODI      | Oswestry disability index                             |
| PROMs    | patient-reported outcome measures                     |
| rCSA     | relative cross-sectional area                         |
| SI       | spine inclination                                     |
| sLSS     | symptomatic lumbar spinal stenosis                    |
| SSA      | spinosacral angle                                     |
| SVA      | sagittal vertical axis                                |
| TK       | thoracic kyphosis                                     |

## 1. BACKGROUND AND PROJECT RATIONALE

Lumbar spinal stenosis (LSS) is a common syndrome affecting the human spine characterized by age related degeneration of the lumbar discs, facet joints (FJs) and hypertrophy of the ligamentum flavum resulting in pain, limited function and compromised quality of life. Symptomatic LSS (sLSS) is an often highly disabling condition [6], the most common reason for spinal surgery in patients older than 65 years of age [7, 8] and represents a major financial burden to the health care system [9]. sLSS has been associated with disability [10], atrophy and fatty infiltration of paraspinal muscles [11], decreased physical activity [12], walking capacity [10], gait patterns and stability [13-15], balance [16] and alterations of the sagittal balance of the spine [17]. However, the natural course and the pathophysiological processes of LSS are not yet fully understood.

The spine's overall function is determined by the interrelationship between the pelvis, the sacrum and the local lumbar, thoracic and cervical spinal curvatures. In a healthy spine, the local curvatures result in a physiological alignment requiring minimal muscular activity for maintenance of upright stance. This state is called global spinal balance. In this state, global and local spinal loads during static posture and dynamic motion will have minimal effects on the spinal canal. However, spinal balance and loads altered by the presence of sLSS may result in further narrowing of the spinal canal and compression of the neural elements or in overloading of the already degenerated lumbar segments possibly eliciting typical pain symptoms. Clinical observations have shown the presence and intensity of symptoms depending on the body posture (e.g., exacerbated while standing, relieved while sitting or lying) or activity (e.g., exacerbated while walking, and relieved while forward bending) [18]. These observations indicate an influence on function and the relevance of physiological loads. Hence, understanding the interrelationship between spinal load, kinematics and functional disability is one of the key factors in the prevention of this disease. Although these observations clearly show that spinal motion and loading plays a critical role in clinical presentation of lumbar spinal stenosis, to date dynamic *in vivo* loads acting on the spine during activities of daily living in patients with sLSS are largely unknown. As an alternative to invasive *in vivo* measurement of spinal loads, computational modelling methods allow for non-invasive investigation of spinal loads *in silico* [1, 19-21].

In the proposed project, we will assess sagittal spinal balance and motion in patients with sLSS using an optoelectronic method based on infrared cameras and retroreflective markers. We will elicit paraspinal muscle fatigue using a modified version of the Biering-Sørensen test and compare sagittal spinal balance and motion before and after the fatigue exercise, which will allow to associate sLSS-specific motion patterns to paraspinal muscle fatigue. Additional data generated using magnetic resonance imaging (MRI) allows detecting associations between sLSS, muscle degeneration and fatty infiltration. Moreover, we will obtain radiological images from the spine in upright position using EOS, a specialized low-dose x-ray unit. In addition we will obtain optical 3D captures (3D back surface reconstructions with Artec EVA) of the back shape of the patients in upright position. The radiographic images and the 3D optical captures of the back shape will allow the calculation of the anatomical global and local sagittal spinal balance, enabling a characterization of spinal kinematics in patients with sLSS and a validation of the workflow based on the optoelectronic method. Coded data obtained from EOS and motion analysis will allow optimizing existing biomechanical musculoskeletal models of the human spine.

The results of this study will provide first mechanistic evidence of the role of clinical, radiological, functional and biomechanical factors in spine load. The combination of *in vivo* experiments with *in silico* experiments represents a unique opportunity of translating knowledge gained from systematic experiments considering biological measurements back to the patient. Confirming the relationship between clinical, radiological, functional and biomechanical factors and local load will provide the necessary evidence for using the framework employed in this project for diagnostics, treatment and rehabilitation planning in patients with LSS and predicting the outcome of existing and novel therapies. The recommendations based on our results will directly impact the treatment of patients at our clinic by identifying patient-specific parameters responsible for large local loads that will allow targeting therapy specifically at these parameters facilitating patient specific evidence-based medicine and ultimately reduce the risk of recurrences of symptoms and/or stenosis after surgery.

## 2. PROJECT OBJECTIVES AND DESIGN

### 2.1 Hypothesis and primary objective

The primary objective of this study is to improve the understanding of the role of postural and ambulatory biomechanics for symptoms in patients with sLSS.

#### Primary hypothesis

Hypothesis 1: PROMs correlate with dynamic compensation (difference between static and dynamic sagittal spinal alignment) in patients with sLSS.

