### 2.2 Primary and secondary endpoints

#### *Primary endpoints*

- I. Oswestry disability index (ODI)
- II. Dynamic compensation

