### II. Dynamic compensation

Dynamic compensation is defined as the difference between static and dynamic sagittal spinal alignment. Six possible gait events are available to choose from for the definition of dynamic sagittal spinal balance (left and right; heel-strike, toe-off, midstance). Dynamic sagittal spinal balance may be defined as sagittal spinal balance during left/right midstance, left/right heel strike and/or left/right toe off. Depending on the research question, we will adapt the workflow and use the most appropriate gait event to calculate dynamic sagittal spinal balance.

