## 4 STATISTICS AND METHODOLOGY

### 4.1 Sample size calculation

To determine if PROMs correlate with dynamic compensation considering categorical covariates with 3 levels of the covariate a sample size of 111 (37 within each level) is required to detect a correlation of 0.3 at 80% power and 5% significance level. Considering a 10% drop-out rate, 122 subjects will be enrolled in the study.

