### 4.2. Statistical analysis plan

Baseline variables will be reported using mean and standard deviation, or median and interquartile range for continuous variables, and as counts and percentages for the categorical variables. Correlation analysis will be used for analysing the association between PROMs and continuous variables, including dynamic compensation, spinal imbalance, segmental instability, muscle degeneration and fatigue, and biomechanical parameters. For measuring the association between categorical variables (e.g., the severity of stenosis) and PROMs, we will perform an analysis of variance (ANOVA). Pre- to postoperative differences in PROMs, dynamic compensation, the severity of stenosis, spinal alignment, segmental instability, muscle degeneration, muscle fatigue, and biomechanical parameters will be assessed by comparing means using paired t-tests for continuous variables, and by comparing frequencies using the chi-square test for the categorical variables. Associations of pre- to postoperative changes in PROMs with changes in static and dynamic spinal imbalance, muscle fatigue, and extent of forwarding trunk bending and lumbopelvic range of motion during walking from before to after spinal stenosis operation will be assessed by computing the difference for each variable from before and after surgery for each patient and evaluating the correlation between these computed differences. The statistical methods described here assume the normal distribution of all parameters. In case of

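### The H1 correlation of ODI with a static–dynamic difference score is a valid test of that difference, but it cannot show whether a result comes from standing posture or from the change during walking

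*Protocol*

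**What the plan says.** The primary objective (protocol 2.1) is to "improve the understanding of the role of postural and ambulatory biomechanics for symptoms in patients with sLSS". The primary hypothesis is that "PROMs correlate with dynamic compensation (difference between static and dynamic sagittal spinal alignment) in patients with sLSS". ODI and dynamic compensation are the two primary endpoints in 2.2, and section 3.3 (II) repeats the definition: "Dynamic compensation is defined as the difference between static and dynamic sagittal spinal alignment".

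Section 4.2 gives the method: "Correlation analysis will be used for analysing the association between PROMs and continuous variables, including dynamic compensation, spinal imbalance" and other parameters, each taken singly. Section 4.1 sizes the study "To determine if PROMs correlate with dynamic compensation considering categorical covariates with 3 levels of the covariate", but the covariate is categorical and is not named. Nothing in the protocol enters static alignment into the H1 test. Alignment and dynamic compensation appear together as explanatory variables only in Hypothesis 2.5 and the prediction model of 4.2, both of which concern postoperative outcome.

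**The concern.** Write S for static alignment, D for dynamic alignment and C = S − D. The protocol does not fix the sign, and a two-sided test does not depend on it. The null hypothesis of the H1 test is cov(ODI, S) = cov(ODI, D). That differs from saying that what happens between standing and walking is unrelated to symptoms once standing posture is known.

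Two things follow. If ODI is related to standing posture only, C can still correlate with ODI, because C contains S. If a worse standing posture and a worse walking posture both go with higher ODI, their contributions to C have opposite signs and offset each other.

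A significant H1 could then be read as evidence about gait when it reflects standing posture, and a null H1 could hide a dynamic relation. This matters because the protocol's rationale is to identify patient-specific parameters at which therapy can be aimed. The separate correlation with spinal imbalance in 4.2 does not settle it: two marginal correlations, read side by side, are not an estimate of one component given the other.

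**Working it through.** **Inputs from the protocol.** N = 111, correlation 0.3, power 80%, significance level 5% (4.1). Sidedness is not stated; two-sided is assumed.

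**Inputs not in the protocol (assumed, with ranges).** ρ = corr(S, D), 0.3 to 0.9. q = SD(D)/SD(S), 0.5 to 1.5, with 1 as base case. r_S = corr(ODI, S), 0.3 to 0.5. Measurement is error-free unless stated.

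**The plan's own figure.** Section 4.1 says that "a sample size of 111 (37 within each level) is required to detect a correlation of 0.3 at 80% power and 5% significance level". By Fisher z, a simple correlation needs n = ((1.960 + 0.842)/atanh 0.3)² + 3 ≈ 85. At n = 111 the power for r = 0.3 is about 90%. The figure of 111 is reproduced by an F test of a three-level factor with f = 0.3 (power 80.3%). That mismatch is a separate matter. Here it means only that N is not short for the H1 correlation.

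**Step 1: ODI depends on static alignment only.**

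corr(ODI, C) = r_S(1 − ρq)/√(1 + q² − 2ρq), which at q = 1 is r_S√((1 − ρ)/2).

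For example, r_S = 0.3 and ρ = 0.5 give 0.3 × √0.25 = 0.15. Chance of a significant H1 at n = 111:

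| ρ | r with C (r_S = 0.3) | significant | r with C (r_S = 0.5) | significant |
|---|---|---|---|---|
| 0.5 | 0.150 | 35% | 0.250 | 76% |
| 0.7 | 0.116 | 23% | 0.194 | 53% |
| 0.8 | 0.095 | 17% | 0.158 | 38% |
| 0.9 | 0.067 | 11% | 0.112 | 22% |

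In simulation, the test of D given S rejects about 5% of the time in this setting.

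**Step 2: sensitivity to the SD ratio (r_S = 0.3, ρ from 0.5 to 0.9).** At q = 0.5 the chance is 79% to 85%. At q = 1.5 it is 5% to 32%, and the sign reverses at ρ of 0.7 and above. If D equals S plus independent variation, then ρq = 1, the correlation with C is zero and the effect vanishes.

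**Step 3: static and dynamic effects in the same direction.** Let ODI correlate 0.3 with S and 0.3 with the part of D that S does not explain, with q = 1. Then

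corr(ODI, C) = 0.3[(1 − ρ) − √(1 − ρ²)]/√(2 − 2ρ).

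| ρ | r with C | power of H1 test |
|---|---|---|
| 0.5 | −0.110 | 21% |
| 0.7 | −0.160 | 39% |
| 0.8 | −0.190 | 51% |
| 0.9 | −0.225 | 66% |

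The partial correlation of ODI with D given S is 0.3/√(1 − 0.09) = 0.314, with power of about 92% throughout.

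**Step 4: the difference itself drives ODI (r = 0.3 with C, q = 1).** The H1 test has about 90% power at every ρ. The test of D given S has 74%, 80%, 84% and 88% at ρ = 0.3, 0.5, 0.7 and 0.9.

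**Step 5: static alignment measured with error (assumed reliability 0.8), D error-free, ODI dependent on true static posture only.** With W the measured static value, corr(ODI, W) = r_S√0.8, corr(W, D) = ρ√0.8 and corr(ODI, D) = r_Sρ. The test of D given W then rejects 9% (ρ = 0.7) and about 17% (ρ = 0.9) at r_S = 0.3, and 18% and 43% at r_S = 0.5. At ρ = 0.9 the unadjusted H1 test rejects less often, 8% and 12%.

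**The case against.** The strongest reply is that nothing here is a false positive. H1 is a statement about the difference, and 4.2 tests the correlation with the difference. In step 1 that correlation is truly non-zero, so rejecting is correct for H1 as worded; in step 3 it is truly weak. This stands. A reader might infer that the H1 test is invalid or has an inflated error rate; the documents do not support that, because the test matches the hypothesis as stated.

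A reader might also infer that the adjusted test should replace the H1 test. That does not follow either. Regressing ODI on C and S is algebraically the same as regressing it on D and S, so the adjusted coefficient concerns dynamic alignment at a given standing posture and not the named primary endpoint. It loses power when the difference itself matters (step 4), and error in static alignment weakens its protection (step 5).

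It also stands that ρ, q and r_S are assumptions. The Background links the diagnosis of sLSS to altered sagittal balance, which does not show that alignment correlates with ODI among patients. Listing spinal imbalance in 4.2 shows only that it will be examined.

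Two replies carry less weight. The separate correlation with imbalance would reveal a static association but not separate it from a dynamic one. The planned model holding both variables addresses postoperative outcome and not H1.

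**Conclusion.** The concern holds as one of attribution. The planned correlation can establish that ODI is associated with the static–dynamic difference. It cannot show whether standing posture or the change during walking is responsible, and the primary objective names both roles.

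In the base case (N = 111, two-sided 5%, equal SDs, no measurement error) with r_S = 0.3, a static association alone makes H1 significant in about 11% to 35% of studies, and same-direction effects of 0.3 leave about 21% to 66% power against about 92% for dynamic given static. These figures illustrate the problem and do not predict its size. Across the SD ratios tried, the static-only figure at r_S = 0.3 runs from about 5% to 85%. The improvement is worth making because it changes what H1 can conclude, at little cost.

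**What to change.** In 4.2, keep the correlation of ODI with dynamic compensation as the H1 test. Prespecify beside it a regression of ODI on static and dynamic alignment of the same alignment parameter (equivalently, on dynamic compensation plus static alignment), and report both coefficients with confidence intervals. State that an H1 result will be described as specific to dynamic compensation only if the joint model supports it. Otherwise it is reported as an association with the difference that static alignment may explain.

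The judgement should rest on the estimates and intervals together, and the adjusted p-value should not be the sole gate, for the reasons in steps 4 and 5.

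Cost: one additional term in a model, using static alignment that the baseline motion capture already records. No further patients, visits or measurements are needed. The price is a second quantity with a different meaning, which the report must explain, and somewhat lower power for it (about 74% to 88% against 90%) if the difference itself is what drives ODI.

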#### Secondary hypotheses

Hypothesis 2.1: PROMs correlate more strongly with quantitative functional parameters including muscle fatigue, spinal load and biomechanical parameters or lumbopelvic range of motion during forward trunk bending and during walking than with pathomorphological parameters including severity of stenosis, segmental instability and muscle degeneration.

Hypothesis 2.2: Changes in PROMs correlate with changes in static and dynamic spinal imbalance, muscle fatigue and extent of forward trunk bending, lumbopelvic range of motion during walking and spinal loads from before to after spinal stenosis surgery.

Hypothesis 2.3: Patients with sLSS with greater muscle degeneration and greater spinal imbalance have greater muscle fatigue.

Hypothesis 2.4: At follow-up, patients with spinal stenosis will have improved PROMs, less static and dynamic spinal imbalance and muscle fatigue, and less forward trunk bending and larger lumbopelvic range of motion during walking than before spinal stenosis surgery.

Hypothesis 2.5: Postoperative PROMs are explained by preoperative severity of LSS, spinal alignment, segmental instability, muscle degeneration, dynamic compensation, muscle fatigue and spinal load.

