violation of this assumption in the data we will use more appropriate statistical methods (e.g., nonparametric methods). Our predictive model building approach will be based on the seven steps of Steyerberg's [45] to construct a predictive model to predict the surgical outcome from preoperative clinical, functional, radiological, and biomechanical data and musculoskeletal model prediction of postoperative local spinal loads. Data will be checked for accuracy, inconsistencies, and plausibility of the recorded information in the data, and if required re-coding/re-grouping of certain variables will be done. We will restrict categorizing the continuous variables in the model development stage as much as possible to avoid loss of information and assess the predictive ability of the clinically relevant variables (e.g., from preoperative – spinal alignment, segmental instability, muscle degeneration, dynamic compensation, muscle fatigue, and biomechanical parameters) and variables with good/high predictive performance will be used to construct the predictive models. A different set of predictive models will be set up using the candidate predictors with the outcome PROMs. We will compare the predictive performance of the models to select the best-performed model using appropriate statistical methods (e.g., R^2). The predictive models will be based on collected experimental data and also simulated data. As a few of the highly clinically relevant variables cannot be measured directly we will use the experimental data to simulate these variables. For the internal validation of the selected predictive model, we will use cross-validation.

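### Hypothesis 2.5 and the modelling text in 4.2 neither name nor require the preoperative PROM as a predictor of the postoperative PROM, so a marker of baseline disability can appear to explain outcome

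*Protocol*

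**What the plan says.** **Hypothesis 2.5 (Protocol 2.1, secondary hypotheses).** "Postoperative PROMs are explained by preoperative severity of LSS, spinal alignment, segmental instability, muscle degeneration, dynamic compensation, muscle fatigue and spinal load". Seven preoperative variables are listed. The preoperative PROM is not one of them.

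**Predictive models (Protocol 4.2).** The aim is "to predict the surgical outcome from preoperative clinical, functional, radiological, and biomechanical data". The candidates are illustrated as "e.g., from preoperative – spinal alignment, segmental instability, muscle degeneration, dynamic compensation, muscle fatigue, and biomechanical parameters", and then "variables with good/high predictive performance will be used to construct the predictive models". On the outcome: "A different set of predictive models will be set up using the candidate predictors with the outcome PROMs". Models are compared on performance, with R² as the example, and the selected model is internally validated by cross-validation. No reference model containing the preoperative PROM is described.

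**Availability (Protocol 3.3).** ODI and the other PROMs are completed at the baseline visit. They come as a separate step after the clinical and demographic parameters (age, body mass, medication, previous treatment, symptom duration and others).

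**Hypothesis 1 (Protocol 2.1).** "PROMs correlate with dynamic compensation (difference between static and dynamic sagittal spinal alignment) in patients with sLSS". Section 4.1 plans for a correlation of 0.3.

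**Hypothesis 2.2 (Protocol 2.1 and 4.2).** "Changes in PROMs correlate with changes in static and dynamic spinal imbalance, muscle fatigue and extent of forward trunk bending", to be assessed by "computing the difference for each variable from before and after surgery for each patient and evaluating the correlation between these computed differences".

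**The concern.** Hypothesis 2.5 is worded as explanation of the surgical result, and section 1 intends the findings to support outcome prediction and the targeting of therapy. For that use, a factor that bears on the result of surgery must be distinguished from one that marks patients who were already worse beforehand. The preoperative value of the same PROM is what separates the two, and nothing in 2.1 or 4.2 guarantees that it enters the model.

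The protocol's own primary hypothesis makes this more than theoretical. If Hypothesis 1 is true at baseline, and pre- and postoperative PROMs are correlated, dynamic compensation will correlate with the postoperative PROM even if it has no prognostic content of its own. Hypothesis 2.5 could then be supported as a by-product of Hypothesis 1.

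Hypothesis 2.2 raises a different and lesser issue. When two variables are correlated at baseline and each regresses toward its mean, their raw changes correlate even if what happens to them afterwards is unrelated.

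**Working it through.** The protocol gives no sample size or expected effect for Hypotheses 2.5 or 2.2, so there is no stated figure to reproduce. The check asks how large the distortion could be.

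**Inputs**
- Correlation of the predictor with preoperative ODI: 0.3, the planning value in 4.1 (a range of 0.2 to 0.5 is also shown).
- Patients at follow-up: 122 × 0.9 = 109.8, from the enrolment and 10% drop-out in 4.1. The formula below uses 109; the simulations use 110.
- Correlation of pre- with postoperative ODI: not in the protocol. Assumed 0.4 to 0.6, with 0.3 to 0.7 as a wider range.
- Two-sided 5% test (4.1 does not state sidedness).

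**Hypothesis 2.5: induced correlation.** Suppose the predictor X has no relation to postoperative ODI once preoperative ODI is known. Then r(X, post) = r(X, pre) × r(pre, post):
- 0.3 × 0.4 = 0.12
- 0.3 × 0.5 = 0.15
- 0.3 × 0.6 = 0.18

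**How often it is declared significant.** By Fisher z, power ≈ Φ(atanh(r) × √(n − 3) − 1.96), with √106 = 10.30:
- r = 0.12: Φ(1.24 − 1.96) = 24%
- r = 0.15: Φ(1.56 − 1.96) = 34%
- r = 0.18: Φ(1.87 − 1.96) = 47%

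**Simulation check** (n = 110, 20,000 replicates, X without any effect given baseline). Share of studies with a significant unadjusted association:

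| r(X, pre) | pre-post 0.3 | pre-post 0.5 | pre-post 0.7 |
|---|---|---|---|
| 0.2 | 10% | 18% | 31% |
| 0.3 | 15% | 35% | 60% |
| 0.5 | 34% | 76% | 97% |

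With the preoperative PROM in the model, the rate is 5% in every cell.

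**Hypothesis 2.2: changes linked only through baseline.** Let X and the PROM correlate r at baseline, let each have stability s from before to after surgery, and let their later variation be independent, with equal variances. The correlation of the raw changes is r(1 − s)² / (2 − 2s) = r(1 − s)/2. At r = 0.3 and s = 0.5 this is 0.3 × 0.5 / 2 = 0.075. In simulation (n = 110) it is significant in 12% of studies. Over r = 0.2 to 0.5 and s = 0.3 to 0.7 the range is 6% to 44%. After adjustment for both baseline values the rate is about 5% (4% to 6%, from 2,000 replicates).

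**The case against.** **The preoperative PROM is not excluded.** A reader might infer that the plan leaves it out. The documents do not support that: the candidate list in 4.2 is given as examples, and the data domains include preoperative clinical data, which could cover PROMs. Section 3.3 lists PROMs apart from the clinical and demographic parameters, so their membership is unclear. If the PROM is a candidate, performance screening would almost surely keep it: at a pre-post correlation of 0.4, Φ(0.424 × 10.30 − 1.96) exceeds 99%. This stands, and the defect is that the PROM is not named or required. A separate analysis plan might name it. But 2.1 fixes the list of explanatory variables and 4.2 fixes how predictors are retained, with no reference model in either place.

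**The 24% to 47% is not the error rate of the planned models.** It belongs to one unadjusted correlation test, whereas 4.2 plans cross-validated models compared on performance. For pure prediction, a variable that carries baseline information is legitimate. This also stands. The figures show how readily such a variable can appear explanatory; they do not show how often the final model would be wrong. The point keeps its force because Hypothesis 2.5 speaks of explanation.

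**Adjustment does not raise power in general.** A gain from 75% to 86% (r = 0.25, pre-post 0.5) holds only for a predictor unrelated to baseline. With r(X, pre) = 0.3 and the same marginal 0.25, the partial correlation is (0.25 − 0.15)/√(0.91 × 0.75) = 0.12, and power is about 24%. That smaller figure reflects the question of added value.

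**Hypothesis 2.2 makes no prognostic claim.** One might extend the same criticism to it. It concerns concurrent changes, the difference already subtracts the baseline PROM, and a stable marker of baseline disability has no systematic change to correlate. Only the regression-to-the-mean issue remains. Correlating changes does answer the hypothesis as worded.

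**Conclusion.** The point holds for Hypothesis 2.5 in this form: the preoperative PROM is neither named nor required, although it is collected and although Hypothesis 1 expects at least one listed predictor to correlate with PROMs. At the protocol's 0.3 and an assumed pre-post correlation of 0.4 to 0.6, a variable with no prognostic value of its own shows a correlation of 0.12 to 0.18 with postoperative ODI. A single unadjusted test finds it significant in roughly 24% to 47% of studies instead of 5%. Those rates rest on an assumed correlation. Even the mildest combination tried (0.2 and 0.3) gives about 10%.

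For Hypothesis 2.2 the problem is separate and smaller: about 12% at middle assumptions, against 35% for Hypothesis 2.5 at the same values.

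Both are secondary hypotheses, so the primary correlation is untouched. The change should still be made, because Hypothesis 2.5 carries the study's claims about surgical outcome.

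**What to change.** **Hypothesis 2.5 (2.1 and 4.2).** State that the preoperative value of the same PROM is a mandatory term in every model for the postoperative PROM, not subject to screening. Report each other predictor's incremental cross-validated R² over the reference model containing that term.

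**Hypothesis 2.2 (4.2).** Keep the raw change-change correlation. Beside it, report a regression of the follow-up PROM on the change in the biomechanical variable, adjusted for the preoperative values of both.

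**Cost.** A change of wording and no new data. Each Hypothesis 2.5 model spends one degree of freedom, and predictors correlated with baseline disability will show smaller apparent effects. The added Hypothesis 2.2 regression spends two degrees of freedom on the baseline terms.
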